### Proposed sample size

Considering this longitudinal design, in the calculation of the sample, we considered a 0.25 effect size, an alpha level of 0.05, a desired statistical power of 0.8, five measures, and three research groups (i.e., control, online intervention, enhanced online intervention). To run a three-level cluster-randomized trial, previous analysis suggested 40 groups per group condition with 15 participants in each, measured at five different time points (see section “Definition of the hierarchical model”).

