### Definition of the hierarchical model

To evaluate the effectiveness of program, a three-level cluster-randomized trial is considered where classrooms are randomly assigned to treatment and control groups. Let *Y*_*tij*_ denote the response at time *t* for *i*th participant (*i* = 1,…, *n*_*j*_) in the *j*th group (*j* = 1, …, *J*), e.g., the *i*th student in the *j*th classroom. The three-level model for longitudinal experiments that involve clustered data is as follows:
1$$ \mathrm{Level}-1:\kern0.5em {Y}_{tij}={\uppi}_{0 ij}+{\uppi}_{1 ij}{T}_{tij}+{e}_{tij},\kern0.5em {e}_{tij}\sim N\left(0,{\sigma}_{et}^2\right) $$2$$ \mathrm{Level}-2:\kern0.5em {\displaystyle \begin{array}{l}{\pi}_{0ij}={\beta}_{00j}+{r}_{0 ij}\\ {}{\pi}_{1ij}={\beta}_{10j}+{r}_{1 ij},\end{array}} $$3$$ {\displaystyle \begin{array}{l}\mathrm{Level}-3:\kern0.5em \begin{array}{l}{\upbeta}_{00j}={\gamma}_{000}+{\gamma}_{001}{G}_j+{u}_{00j}\\ {}{\upbeta}_{10j}={\gamma}_{100}+{\gamma}_{101}{G}_j+{u}_{10j},\end{array}\\ {}\left[\begin{array}{l}{r}_{0 ij}\\ {}{r}_{1 ij}\end{array}\right]\sim N\left[\begin{array}{l}0\\ {}0\end{array}\right],\left[\begin{array}{ll}{\sigma}_{r0}^2& \\ {}0& {\sigma}_{r1}^2\end{array}\right],\left[\begin{array}{l}{u}_{00j}\\ {}{u}_{10j}\end{array}\right]\sim N\left[\begin{array}{l}0\\ {}0\end{array}\right],\left[\begin{array}{ll}{\sigma}_{u0}^2& \\ {}0& {\sigma}_{u1}^2\end{array}\right]\end{array}} $$

Substituting Eqs. 2 and 3 into Eq. 1, we have the mixed model of interest
4$$ {Y}_{tij}={\gamma}_{000}+{\gamma}_{00j}{G}_j+{u}_{00j}+{r}_{0 ij}+{\gamma}_{100}{T}_{tij}+{\gamma}_{101}{G}_j{T}_{tij}+{u}_{10j}{T}_{tij}+{r}_{1 ij}+{e}_{tij} $$

The lowest level variance component is represented by *e*_*tij*_, and the two level 2 variances are as follows: the variability in intercepts across subjects (*r*_*0ij*_) and the variability in slopes across students (*r*_*1ij*_) nested within classrooms. The level 3 variance components are as follows: the variability in intercepts across classrooms (*u*_*00j*_) and the variability in slopes across classrooms (*u*_*10j*_).

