As Heo et al. [54] and others (e.g., [55]) have indicated, the most important goal of a longitudinal intervention is to test whether there are differences between intervention groups with respect to their average growth rates. Applying the approach of these authors, the power to detect a specified treatment difference between average rates of change for the groups is defined as the probability of rejecting the null hypothesis of no treatment-by-linear-trend interaction *H*_0_: γ_101_ = 0, given that it is fact false (γ_101_ ≠ 0). This hypothesis can be tested with
5$$ {F}_o=\frac{{\hat{\gamma}}_{101}^2}{Var\left({\gamma}_{101}\right)}=\frac{\Delta^2\left[{N}_1{N}_2{N}_3 Var(T)\right]}{2\left(1-{\rho}_1\right){\sigma}^2{N}_1 Var(T){\sigma}_{u1}^2}, $$

where Δ is the effect standardized effect size at the last time point, *N*_1_ is the number of level 1 units (repeated measures) per student, *N*_2_ the number of level 2 units (students) per classroom, *N*_3_ the number of level 3 units (classroom) per treatment condition, *Var*(*T*) is the population variance of the time variable *T*, $$ {\upsigma}_{u1}^2 $$ is the three-level random slope variance, σ^2^ is the sum of the other variances, and *ρ*_1_ is the correlation between outcomes measures at different time points on the same student nested within classroom.

The power of the test statistic *F*_0_, denotes 1 − *β*, can be written as follows:
6$$ 1=\beta =\phi \left\{{\left\{\frac{\Delta }{\left({N}_1-1\right)}\left[\frac{\left[{N}_1{N}_2{N}_3 Var(T)\right]}{2\left(1-{\rho}_1\right){\sigma}^2{N}_1 Var(T){\tau}_s}\right]\right.}^{\frac{1}{2}}-{Z}_{1-\left(\alpha /2\right)}\right\}, $$

where τ_*s*_ is the ratio of the three-level random slope variance to the sum of the other variances, ϕ is the cumulative distribution function of a standard normal distribution, and *Z*_1 − (α/2)_ is the 100 (1 − *α*/2) percentile of the standard normal distribution for a bilateral test.

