Consider the following hypothetical values for three-level cluster-randomized trial design parameters: $$ {\upsigma}_e^2=0.5 $$, $$ {\upsigma}_{r0}^2=0.3 $$, $$ {\upsigma}_{r1}^2=0.0 $$, $$ {\upsigma}_{u0}^2=0.2 $$, and $$ {\upsigma}_{u1}^2=0.1 $$. Under the fixed slopes model, the correlation between the outcomes from different student nested within the same classroom is $$ {\uprho}_2={\upsigma}_{u0}^2/\left({\upsigma}_e^2+{\upsigma}_{r0}^2+{\upsigma}_{u0}^2\right)=0.2 $$, whereas the correlation between the outcomes measured at different time points on the same students nested within classrooms is $$ {\uprho}_1={\upsigma}_{r0}^2+{\upsigma}_{u0}^2/\left({\upsigma}_e^2+{\upsigma}_{r0}^2+{\upsigma}_{u0}^2\right)=0.5 $$. Further assumptions are as follows: (a) number of classrooms per treatment condition: *N*_3_ = 40; (b) average number of students per classroom: *N*_3_ = 15; (c) number of repeated measures per student: *N*_1_ = 5; (d) alpha significance level: *α* = 0.05; and (e) statistical power: 1 − *β* = 0.80.

Given design parameters and further assumptions, the minimum detectable effect size is 0.25. In our opinion, an effect size of Δ = .25 is a good first estimate of the smallest effect size of interest in psychological research, since it is not irrelevant and requires a considerable sample size to detect a treatment effect predicted by the researcher.

Finally, we consider that a study with 80% power is a properly powered study, despite several researchers (see, e.g., [56]) consider this a value rather low, as it entails a 20% chance of not finding a theoretically important finding.

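### The detectable effect of 0.25 averages a classroom-level slope variance over students; the model as written gives about 0.81, with about 14% power at 0.25

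*Protocol article*

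**What the plan says.** The Proposed sample size section bases recruitment on a power calculation: "previous analysis suggested 40 groups per group condition with 15 participants in each", with "an alpha level of 0.05, a desired statistical power of 0.8, five measures". The calculation is in Definition of the hierarchical model. The model there has two separate slope deviations, r_1ij for each student and u_10j for each classroom, and describes the latter as "the variability in slopes across classrooms". The text below Eq. 5 repeats the level: σ²_u1 "is the three-level random slope variance". The listed design parameters are σ²_e = 0.5, σ²_r0 = 0.3, σ²_r1 = 0.0, σ²_u0 = 0.2 and σ²_u1 = 0.1. The section then concludes: "Given design parameters and further assumptions, the minimum detectable effect size is 0.25". It goes on to treat 0.25 as a reasonable smallest effect to aim for and 80% power as adequate.

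**The concern.** The only slope variation the plan allows for sits at the classroom. Fifteen students in one classroom share one slope deviation, so adding students cannot average it away; only adding classrooms can. A classroom slope variance of 0.1 with 40 classrooms per arm looks too large for an effect of 0.25 to be detectable.

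This figure is the quantitative basis for 40 × 15 participants per arm. The Statistical analysis plan section makes a significant group-by-time interaction the evidence for a group difference, and that is the test powered here. If true power at 0.25 is far below 80%, the trial would usually miss the effect it was sized for, and a null result could be taken as more informative than it is.

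**Working it through.** **Inputs.** All come from Definition of the hierarchical model and Proposed sample size.

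- N1 = 5 measures, N2 = 15 students per classroom (printed with the symbol N3, evidently a slip), N3 = 40 classrooms per arm.
- σ²_e = 0.5, σ²_r0 = 0.3, σ²_r1 = 0, σ²_u0 = 0.2, σ²_u1 = 0.1. The variances other than the classroom slope sum to σ² = 1.0, and ρ1 = 0.5.
- Two-sided α = 0.05 and power 0.80, so z = 1.960 + 0.8416 = 2.8016.
- Time coded 0 to 4, so Var(T) = 2. This coding is inferred from the factor (N1 − 1) in Eq. 6.
- Effect 0.25 at the last time point, so the slope difference is 0.25/4 = 0.0625 per step.

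**Step 1: reproduce 0.25.** As they appear in the text at hand, Eqs. 5 and 6 have a product in the denominator. Taken literally, this gives a detectable effect of 0.145. A plus sign may have been lost when the text was read from the PDF, so this is not held against the plan. With the two terms added:

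- Var = 2[(1 − ρ1)σ² + N1·Var(T)·σ²_u1] / (N1·N2·N3·Var(T)) = 2(0.5 + 5 × 2 × 0.1) / (5 × 15 × 40 × 2) = 3/6000 = 0.0005
- SE = 0.02236
- Detectable effect = 2.8016 × 0.02236 × 4 = **0.2506**; power at 0.25 is **79.8%**

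This is the plan's figure. In this expression the slope term reduces to 2 × 0.1/(N2·N3) = 2 × 0.1/600, so the variance is averaged over students.

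**Step 2: the model as written.** A classroom-level slope averages over N3 only:

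- Var = (2/N3)[σ²_u1 + σ²_r1/N2 + σ²_e/(N1·N2·Var(T))] = (2/40)(0.1 + 0 + 0.5/150) = 0.005167
- SE = 0.07188
- Detectable effect = 2.8016 × 0.07188 × 4 = **0.806**
- Power at 0.25: 0.0625/0.07188 = 0.870; Φ(0.870 − 1.960) = 0.138, plus a lower tail of 0.002, gives **14.0%**

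**Step 3: confirmation.** Exact generalised least squares on the full 75 × 75 classroom covariance matrix gives the same SE, 0.07188. Moving the 0.1 to student level (σ²_r1 = 0.1, σ²_u1 = 0) gives 0.02236, the plan's value. Simulated power at 0.25 under the model as written was 13.6% (20,000 simulated trials, t test on classroom slopes).

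**Step 4: sensitivity.**

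| Setting | Detectable effect | Power at 0.25 |
|---|---|---|
| σ²_u1 = 0.1, σ²_r1 = 0 (as stated) | 0.81 | 14% |
| σ²_u1 = 0.05, σ²_r1 = 0 | 0.58 | 23% |
| σ²_u1 = 0.01, σ²_r1 = 0 | 0.29 | 68% |
| As stated, but four measures | 0.61 | 21% |

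- With unlimited students per classroom, the detectable effect is still 4 × 2.8016 × √(2 × 0.1/40) = 0.79. No class size reaches 0.25.
- A detectable effect of 0.25 needs Var = (0.0625/2.8016)² = 0.000498, so σ²_u1 = 20 × 0.000498 − 0.0033 = 0.0066.
- At the stated values, 80% power at 0.25 needs 2(0.1 + 0.5/150)(2.8016/0.0625)² = 415.3, that is 416 classrooms per arm.

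**The case against.** The strongest reply is that 0.1 was meant as the student slope variance and two subscripts were exchanged. Then 0.25 is exact. This is plausible: a classroom slope variance of 0.1 implies a classroom SD of √0.1 × 4 = 1.26 at the last time point, more than the total SD of 1.0 from all other sources. The values are also called hypothetical. But the model definition, the text under Eq. 5 and the parameter list all place the 0.1 at the classroom. If the labels are wrong, the calculation rests on a classroom slope variance of zero that is nowhere stated. Calling the inputs hypothetical does not make the result derived from them correct.

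Three further points stand but do not rescue the figure:

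- The plan's formula used above is the reading that yields 0.25, not a literal transcription.
- Table 3 and the outcome section list four assessments, not five. With four, the detectable effect is 0.61 and power at 0.25 is 21%.
- If the effect were standardised by the total SD at the last time point, √(1.0 + 16 × 0.1) = 1.61, the detectable effect would be 0.806/1.61 = 0.50 and power at 0.25 about 29%. Eq. 6, which scales by the other variances, points away from this reading.

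The Discussion does concede a small sample and the possibility of smaller effects than anticipated. It then offers the a priori power analysis as mitigation, and that analysis is the one in question.

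**Conclusion.** The concern holds and needs correcting. For the parameters the protocol lists, the minimum detectable effect is about 0.81, roughly 3.2 times the stated 0.25 (0.806/0.25), and power at 0.25 is about 14%, so the effect would be missed about 86% of the time. This assumes equally spaced times coded 0 to 4, complete data, a single two-arm contrast at two-sided 0.05, and the slope variance at the level the protocol gives it. None of the alternative readings of the number of measures or the scale of the effect brings power near 80%. Only moving the 0.1 to student level does so, and that contradicts the text. The section on randomization allocates whole schools; any variation between schools would lower power further, but the protocol gives no figure for it.

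**What to change.** Replace the variance behind Eqs. 5 and 6 with

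Var(γ_101) = (2/N3)[σ²_u1 + σ²_r1/N2 + σ²_e/(N1·N2·Var(T))]

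and then take one of two routes.

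1. **If the listed values are intended**, restate the result as a detectable effect of about 0.81, with about 14% power at 0.25.
2. **If 0.1 was meant as the student slope variance**, relabel it σ²_r1 = 0.1 and report detectable effects over a range of classroom slope variances, with a reason for the range chosen. With σ²_r1 = 0.1 and the multiplier 2.8016 × 4 = 11.206:
   - σ²_u1 = 0: 11.206 × √(0.05 × 0.0100) = 0.25
   - σ²_u1 = 0.01: 11.206 × √(0.05 × 0.0200) = 0.35
   - σ²_u1 = 0.1: 11.206 × √(0.05 × 0.1100) = 0.83

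On either route, say that the figure refers to one pairwise contrast at unadjusted 0.05 in a three-arm trial. Carry the restated figure into Proposed sample size and into the Discussion's remark on power.

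The cost is rewriting two equations and one paragraph, and a less favourable power statement. No extra enrolment or change in conduct is asked for.

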### Blinding and data access

The assessment protocol will be completed by children on-site and will not be available for parents to consult or to the educational psychologist conducting the sessions. Each child will be attributed a unique code. Moreover, data will be analyzed by an external statistician who will be blind to the research groups of each data set. Additionally, only the principal investigator and the statistician will have access to the full data set, which will be used only for investigation. Also, all questionnaires will be destroyed once all data are published. Lastly, the procedures for personal data storage, handling, and protection will comply with the newest GDPR (General Data Protection Regulation) policies. Particularly, to ensure privacy and anonymity, pseudonymization will be carried out. This is a process that transforms personal data into a data set that cannot be linked to a particular subject unless another piece of information is added (e.g., decryption key). Usually, these data are stored in different locations.

### Data monitoring and trial management

The trial will be supervised by a Trial Steering Committee (TSC) directed by the principal investigator (PI) of the trial. The TSC will meet every 4 months to monitor the trial progress, as well as review and manage the data. Besides the PI, the TSC will also include two independent researchers, one educational psychologist and a methodology expert, who are not directly involved in the study, and the CoPI. An independent statistician with no involvement in the trial will conduct all the data analysis and will inform the results to the TSC at a joint meeting. The co-investigators and research assistants of the project will be responsible for all aspects of local organization of the trial (e.g., identify potential recruits, take consent). To ensure the protocol is implemented as planned, the PI will be responsible for managing and supervising the trial and providing direction and administrative support. Three general meetings with the entire group of researchers will be held throughout the project and smaller monthly meetings will be conducted between the PI, the CoPI, and the researchers to monitor the development of activities and ensure compliance with the goals. Lastly, regular meetings will be conducted between the PI, the science manager, and the financial manager of the research center.

This trial does not have a Data Monitoring Committee (DMC) as the current trial is a low-risk intervention, without safety issues or foreseen risks associated. Moreover, the trial does not have a Stakeholder and Public Involvement Group (SPIG) as the researchers that will carry the intervention are trained and certified educational psychologists.

### Safety aspects and ethical considerations

The standard procedure to conduct studies and interventions in the Portuguese school context requires an a priori evaluation and validation of the project by the Ministry of Education before researchers can invite schools to participate. Additionally, approval of the Ethics Committee of the University of Minho was obtained and can be consulted on the trial registration. Participation in the program is entirely voluntary, and parents and children are informed that their involvement in the school’s activities will not be affected by their decision on whether or not to participate. Additionally, because there are no anticipated detrimental consequences or real risks for the participants involved in this intervention, we did not include in the current trial interim assessment, stopping rules, nor criteria for discontinuing or modifying allocated interventions. In fact, parents and children are informed they can withdraw from the program at any time. We fully recognize our responsibilities for child protection, so the project must ensure that the children who participate are safe from all forms of abuse, injury, neglect, maltreatment, and exploitation. The project will ensure an environment where children feel secure, feel free to either participate or leave the study at any time, are encouraged to talk, and are listened to. Child welfare is paramount. Hence, children are safeguarded by the adoption of child protection guidelines and by a code of conduct for all involved. In order to work with children, researchers must present their criminal records during the job application. Additionally, parental consent must be obtained before carrying any procedure with children. This protocol will be held to meet high ethical standards.

Lastly, for ethical reasons, once all the assessments have been conducted, the control group will be given the opportunity to receive the intervention. This will guarantee that all children share the same benefits of the program. In this sense, all participants will have the opportunity to develop not only knowledge but also a set of transversal skills and strategies on the healthy habits’ domain. The participation in this intervention will bring no harm, and no risks were identified. Therefore, there will be no compensation for trial participation, and no post-trial care for participants is anticipated.

### Dissemination

The plan for disseminating the research outcomes of the HEP-S program include the following: (a) write and publish papers in peer-reviewed journals, including the efficacy of the intervention program; (b) write a document systematizing guidelines for online interventions focused on the promotion of healthy eating through SRL; (c) conduct workshops about implications for practice targeting participants (both children and caregivers), educators, health professionals, and relevant stakeholders; and (d) organize advocacy groups comprised of children, parents, teachers, and the health community to advocate for the importance of launching policies on healthy eating habits. Advocacy groups for healthy eating habits could consider working with governmental agencies and food companies to help set environmental and structural changes likely to facilitate individual healthy choices. The work done by these advocacy groups is expected to generate public debate on this issue and, hopefully, help flourish innovative strategies to prevent obesity.

## Discussion

Prevention of overweightness and obesity remains poorly effective, representing a great challenge and a major concern for governments and relevant stakeholders worldwide. Despite the numerous efforts carried to mitigate this major health issue, overweightness and obesity do not seem to be diminishing [1]. There is, therefore, a pressing need to provide evidence-based options to improve healthful eating among individuals of all ages, particularly among children.

This study will develop and evaluate a preventive online-based intervention to promote the development of self-regulation skills for healthy eating among elementary school children. Although many online preventive interventions regarding healthful lifestyles have been developed, seldom the approaches have focused on children or skill development. Moreover, although the program has children as the target population, parents and families will be deeply involved throughout the intervention. All these aspects confer to this intervention a unique and innovative character.

An online-based intervention will, expectedly, help overcome some challenges associated with the implementation of school-based programs. For instance, educational psychologists are still a scarce resource at the school setting, being often difficult to develop programs of preventive nature instead of remedial ones. Thus, it is aimed that HEP-S helps narrow the gap between children and their access to preventive, skill promotion, psychoeducational programs, in a cost-effective format by providing at-distance support to several groups of children. This strategy allows allocating human resources more effectively as, often, an education psychologist is responsible for several schools within the same district. Furthermore, it is expected that by actively involving parents in the intervention, adherence and engagement raises. Thus, we believe the HEP-S program may play an important role in preventing risky and unhealthy eating behaviors and contribute to more healthful lifestyles within families.

This study has some strengths worth highlighting. First, it presents an online-based intervention focused on promoting SR skills and strategies to promote healthy eating behaviors among elementary school-aged children. Second, it is conceived as a preventive approach, focused on promoting health-related behaviors, not on treatment. Third, gamification strategies will be implemented to reduce high rates of attrition and low feelings of engagement with the tool. Lastly, the research design foresees an implementation period longer than most of the intervention studies in this domain, with long follow-up. This will allow searching for sustained behavioral changes as a result of the intervention.

There are potential limitations to the present study proposal. First, although we include a weekly journal for participants to complete, during the study it will be difficult to monitor the actual implementation of the strategies trained in the program. Second, full adherence to the program will be a challenge as it implies some level of parental involvement and it lasts for 20 weeks. Third, although the study design is optimized by the selection of relevant psychological variables and the introduction of gamification strategies, the small sample size of this study confers a limited scope to examine full effects. In fact, there is the possibility that smaller effects than anticipated are found. This particular aspect may pose limitations when reflecting about the implications and conclusions of the study. Nevertheless, the study attempts to minimize this aspect by having conducted a priori power analyses. If the present trial shows positive effects at the primary outcomes level, future trials should try to use larger samples, from distinct backgrounds and cultures and include longer follow-up measures (> 6 months).

Altogether, we expect that the results of this study will provide evidence on whether training and fostering SR strategies among elementary school-aged children helps in the promotion of healthy eating habits.

